**Methods/design:**

A RCT will be conducted to compare the efficacy of GET.ON Mood Enhancer with an active control condition receiving online psychoeducation on depression (OPD). Both treatment groups will have full access to treatment as usual. Adults with MDD (*n* = 128) will be recruited and randomised to one of the two conditions. Primary outcome will be observer-rated depressive symptoms (HRSD-24) by independent assessors blind to treatment conditions. Secondary outcomes include changes in self-reported depressive symptom severity, anxiety and quality of life. Additionally, potential negative effects of the treatments will systematically be evaluated on several dimensions (for example, symptom deteriorations, attitudes toward seeking psychological help, relationships and stigmatisation). Assessments will take place at baseline, 6 and 12 weeks after randomisation.

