### Sample size calculation

We aim to include 128 participants. This sample will allow us to detect a between-group effect size (ES) of d = 0.50 with a power (1-ß) of 80% and an alpha of 0.05 (calculated using PASS 12). The most recent meta-analytic review found a mean ES of d = 0.78 for therapist-supported web-based interventions for depression [19]. However, most of the included studies used a waiting-list control comparison only, and these studies showed a considerably larger ES than those studies including a treatment-as-usual condition. Our comparison condition will include psychoeducation and full access to treatment as usual and participants are encouraged to seek further help. Thus, we expect a somewhat smaller ES of d = 0.50 at post-treatment.

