### Statistical analyses

The clinical trial will be conducted in compliance with the Declaration of Helsinki, the CONSORT guidelines, GCP and the protocol. Aiming at an intention-to-treat design [61] we will include all participants who will be randomly assigned to one of the two conditions. Additional per protocol analyses (PPA) will be conducted, including only participants’ satisfying protocol treatment (completed at least 4 of 6 modules). Mixed-model analyses of variance will be conducted to explore the effects of the treatments on all continuous outcomes. Missing data will be handled using multiple imputations (MI). MI is especially robust with respect to missing data [62]. Nevertheless, to assess systematic effects of non-ignorable missing data, pattern mixture analyses for multi-level longitudinal approaches [63] will be conducted. To determine if the treatment effect is dependent on missing data, the missing-data pattern of each participant will be first coded and then included in a three-way interaction (missing pattern × condition × change in depression severity) in the main outcome analyses. If no significant interactions between missing-data pattern and treatment outcome are found, we will conclude that no missing data bias occurred in the results. For all mixed-model analyses, Cohen’s d [64] will be calculated by standardising the differences between baseline and follow-up scores by the pooled standard deviation of the baseline scores. Response and remission rates will be compared across groups with the help of contingency tables and χ2 tests. We will also calculate the number needed-to-be-treated (NNT) with GET.ON Mood Enhancer to achieve one response and remission, respectively, compared to the control group. We will also calculate the number needed-to-harm, which indicates the number of participants treated in the experimental condition for one extra person to have a symptom deterioration. Because the differential risk of the intervention ideally needs to be set into relation with its benefits we will also calculate a benefit-risk ratio [65]. Benefit-risk ratio will be calculated by dividing the NNH to achieve one symptom deterioration through the NNT to achieve one response. If this benefit-risk ratio is greater than 1, the benefits outweigh the risks; if it is 1, the balance between benefit and risks are equal across the groups; if it is less than 1, the risks outweigh the benefits (LIT). Benefit-risk ratios will only be calculated when differences in risk for symptom deteriorations are statistically significant.

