Overall, to overcome the gap between the need for treatment and evidence-based treatment availability and treatment utilisation, (cost-) effective low-threshold interventions are needed that are accessible for as many people as possible. Internet-based guided self-help interventions might be a promising strategy not only as a first step in a stepped-care approach but by providing treatments that are more intensive when patients fail to respond. If at some point this strategy becomes classified as evidence-based treatment, such approaches could provide evidence-based services to patients in areas or countries where psychotherapeutic treatment is not readily available [66]. If the proposed trial shows that the investigated intervention is not only effective in reducing depressive symptoms but also shows an acceptable risk-benefit balance, it would further strengthen the arguments for a wide dissemination of Internet-based guided self-help approaches for Major Depression.

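### The benefit-risk ratio is triggered by a significant deterioration difference in either direction, but its below-1 verdict is wrong or undefined when GET.ON reduces deterioration

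*Protocol article*

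**What the plan says.** The Statistical analyses section of the protocol article sets out the benefit-risk summary in four steps.

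- NNT is the number treated with GET.ON Mood Enhancer for one response (and, separately, one remission) compared with control.
- NNH is described in words, as the number treated in the experimental arm per additional patient who deteriorates.
- The benefit-risk ratio is NNH for deterioration divided by NNT for response. Above 1 favours the treatment and exactly 1 is balance. Below 1 the reading is: "if it is less than 1, the risks outweigh the benefits".
- The ratio has a trigger: "Benefit-risk ratios will only be calculated when differences in risk for symptom deteriorations are statistically significant". No direction is attached to it.

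Nothing is said about a negative or undefined NNH or NNT. The Negative effects section defines deterioration as reliable worsening on the HRSD-24, the primary outcome scale. The Discussion makes part of the case for wide dissemination depend on whether the intervention "shows an acceptable risk-benefit balance".

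**The concern.** A ratio of NNH to NNT has a clear meaning only when the treatment produces both more responses and more deteriorations than control. The article's trigger is wider than that: a significant reduction in deterioration satisfies it too. The trial expects a greater fall in HRSD-24 under GET.ON than under psychoeducation, and deterioration is reliable worsening on that same scale. Fewer deteriorations under GET.ON is therefore the direction one would expect if the main hypothesis is right. In that case the rule either gives the wrong verdict or has nothing to evaluate.

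The trigger also raises a second, separate issue. A ratio reported only after a significant test is missing whenever the test fails, and when it does appear it rests on a difference selected for being large. The sample was sized for depression severity, not for deterioration.

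The ratio is the only formal rule the article gives for weighing benefit against harm, and negative effects are one of its stated emphases.

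**Working it through.** **Inputs from the article.** Total sample: "We aim to include 128 participants". Design effect: "detect a between-group effect size (ES) of d = 0.50", with power "of 80% and an alpha of 0.05 (calculated using PASS 12"). Analysis set: "we will include all participants who will be randomly assigned to one of the two conditions". Significance level 0.05 throughout.

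**Assumptions.** The allocation ratio is not stated; participants "will be recruited and randomised to one of the two conditions", and I take 1:1, so 64 per arm, all analysed. The article gives no deterioration or response rates, so every rate below is assumed. It names the chi-square test for response and remission; I assume the same test for deterioration and show Fisher's exact test alongside.

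**The plan's own figure.** A two-sided t-test with d = 0.50 and 64 per arm has 80.1% power (79.5% with 63), so 128 reproduces. That calculation concerns depression severity only.

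**Sign of the ratio.** Write RD for the risk in GET.ON minus the risk in control. Then NNT = 1/RD(response), NNH = 1/RD(deterioration), and the ratio is NNH/NNT.

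*Example with counts.* Deterioration 1/64 in GET.ON and 9/64 in control.

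- Chi-square = 128 × (1×55 − 9×63)² / (10 × 118 × 64 × 64) = 6.94, p = 0.008. The trigger is met. Fisher's test is also met, since it needs only 8 against 1.
- RD = 1/64 − 9/64 = −0.125, so NNH = −8.
- With an assumed NNT of 5, the ratio is −8/5 = −1.6, which is below 1.

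*Examples with rates.*

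| Response, GET.ON vs control | Deterioration, GET.ON vs control | NNT | NNH | Ratio | Verdict under the rule |
|---|---|---|---|---|---|
| 50% vs 30% | 5% vs 20% | 5.0 | −6.7 | −1.33 | risks outweigh |
| 50% vs 30% | 20% vs 5% | 5.0 | 6.7 | 1.33 | benefits outweigh |
| 40% vs 30% | 5% vs 20% | 10.0 | −6.7 | −0.67 | risks outweigh |

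The first two rows have the same response gain. The one in which GET.ON also protects against deterioration gets the adverse label, and the one in which it causes deterioration gets the favourable label. Absolute values do not repair this: in the third row |NNH|/NNT = 6.7/10 = 0.67, still below 1, although GET.ON is better on both counts.

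**Which direction meets the trigger.** With 5% under GET.ON and 10% under control, exact enumeration shows that 99% of significant results have fewer deteriorations under GET.ON.

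**How often the trigger is met.** Exact binomial enumeration, 64 per arm:

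| Assumed rates | Chi-square | Fisher |
|---|---|---|
| 3% vs 6% | 12% | 4% |
| 5% vs 10% | 19% | 10% |
| 10% vs 20% | 35% | 27% |
| 5% vs 15% | 49% | 36% |
| 5% vs 20% | 76% | 67% |
| 1/64 vs 9/64 | 82% | 68% |

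**Selection.** At 5% vs 10%, the mean absolute difference among significant results is 11.5 points against a true 5, and 11.5/5 = 2.3-fold. At 1/64 vs 9/64 it is 13.9 against 12.5, or 1.1-fold.

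**Harmful direction.** With 3/64 deteriorating in control, 9/64 under GET.ON gives p = 0.069 and no ratio; 10/64 gives p = 0.041 and a ratio. A tripled count would not bring the ratio into the report.

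**The case against.** **NNH is undefined when nobody extra deteriorates.** The article defines NNH in words and prints no signed formula. On that reading there is no negative ratio and no wrong label. This is a fair reading, and it limits how firmly one can say the rule mislabels a better treatment. It does not rescue the rule: the trigger still calls for a ratio, and the article does not say what to report instead.

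**The significance condition is a reasonable guard.** When the deterioration difference is compatible with zero, NNH is unstable and its interval runs through infinity. Withholding a ratio then is defensible, and this stands. The condition still leaves the ratio missing or selected when the difference is modest.

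**Two stronger readings are tempting.** A reader might infer that the trigger will rarely be met. The article gives no deterioration rates, and over the assumed scenarios the chance runs from 12% to 82%. A reader might also infer that the trial will usually give no information on the balance. The condition applies to the ratio alone; response comparisons, NNT and NNH are planned whatever the test shows.

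**The two problems do not peak together.** Where the deterioration difference is large enough for the wrong verdict to be a live risk, the trigger is usually met and exaggeration is slight (82% and 1.1-fold at 1/64 vs 9/64). The 19% and 2.3-fold figures belong to a smaller difference, where the ratio would mostly not be computed. They should not be combined into one worst case.

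**It is a secondary item.** Correct: negative effects are evaluated in secondary analyses, and the ratio is one derived summary of them.

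**Conclusion.** The point holds in two parts of unequal weight.

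First, the trigger is two-directional while the verdict makes sense in one direction only. For a significant reduction in deterioration, the stated rule gives a ratio below 1 and the wrong conclusion (signed NNH), or a ratio that cannot be computed (NNH undefined). The defect follows from the wording and does not depend on the assumed rates; only the size of the examples does.

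Second, and less certain, the ratio will often be missing unless the deterioration difference is large, and can be exaggerated when it appears. How often depends wholly on rates the article does not give, and on 64 analysed per arm.

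The effect is confined to a secondary benefit-risk summary. The primary HRSD-24 analysis and the sample size are unaffected. It is worth correcting before analysis because the article itself links dissemination to the risk-benefit balance.

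**What to change.** Amend the benefit-risk text in the Statistical analyses section as follows.

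1. Compute the ratio, and apply its above-1 and below-1 reading, only when both NNH and NNT are positive.
2. If deterioration is lower with GET.ON, report the number needed to treat to prevent one deterioration, with no ratio.
3. Report the risk differences for response and for deterioration with 95% CIs, regardless of significance. A significance condition on the ratio then does less harm, because the unselected estimates are always shown.

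I would not replace the ratio with a single net difference (response minus deterioration): it counts one response as equal to one deterioration, a value judgement the article does not make.

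The cost is a few sentences and a small table, with no new data and no change to the sample size. The downside is that wide intervals will be in plain view.

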##### Other adverse events

Other adverse events will be measured with the negative effects of psychotherapy inventory (INEP). The INEP is a relatively new measure and was developed for assessing systematic and potentially negative effects of psychotherapeutic interventions in different domains. The version used in this study consists of 15 items assessing any negative effects participants experienced within or after the completion of the Internet-based training on (1) negative intrapersonal changes (for example, ‘During treatment or since the end of my therapy, I suffered from suicidal thoughts or intentions for the first time ever’), (2) negative effects in an intimate relationship (for example, ‘My partner is or has been jealous of my therapist’), (3) family/friends (for example, ‘The relationships with my friends has worsened’), (4) perceived dependence on the psychotherapist/psychotherapeutic intervention (for example, ‘I feel dependent on my therapist’), and (5) stigmatisation (for example, ‘I am anxious that my colleagues or friends could find out about my psychotherapy’). The items are rated on a 4-point Likert scale (0 = no agreement at all; 3 = total agreement). Chronbach’s alpha is α = 0.85 (Table 2).

**Table 2 T2:** Overview of measurements

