
For other negative effects, we will use independent t-tests for continuous, χ^
*2*
^ for categorical, and logistic regression for binary outcomes. In a pre-planned subgroup analysis, we will explore negative effects of GET.ON Mood Enhancer on attitudes towards seeking psychological help in patients who do not reach the response criteria up to post-assessment (6 weeks). For all statistical analyses, significance level will be set at *P* <0.05. All analyses will be conducted using SPSS 20.

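### Logistic regression is fixed for binary other negative effects, but it is unreliable if an effect is rare: an empty arm gives an infinite odds ratio, and neither the Wald nor the likelihood-ratio P can be trusted

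*Protocol article*

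**What the plan says.** The Statistical analyses section treats negative effects in two places. Symptom deterioration goes with the number needed to harm and the benefit-risk ratio. All other negative effects are covered by one later sentence: t-tests for continuous measures and χ2 "for categorical, and logistic regression for binary outcomes". The same paragraph sets one threshold for everything ("For all statistical analyses, significance level will be set at" P <0.05) and names SPSS 20 as the software. It does not say which test of the logistic coefficient will be reported, and it names no exact or penalised alternative.

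The instrument is described under Other adverse events: the INEP, with 15 items. One example item reads "I suffered from suicidal thoughts or intentions for the first time ever". On scoring: "The items are rated on a 4-point Likert scale (0 = no agreement at all; 3 = total agreement". The article gives no rule for making items binary and no expected frequency for any of them. On size, the Sample size calculation section says "We aim to include 128 participants".

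**The concern.** Logistic regression fitted by maximum likelihood relies on there being events in both arms. If one arm has none, the likelihood keeps rising as the log odds ratio goes to infinity. No finite estimate exists, and the standard error at which the software stops is an artefact of the iteration limit. The Wald statistic then tends to zero however many events the other arm has.

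With about 64 per arm this could happen for an uncommon effect such as first-ever suicidal thoughts. Negative effects are a stated objective, and the Discussion presents their systematic evaluation as a contribution of the trial. A result such as none against six would be the kind of signal that this part of the trial exists to find. The planned model would return no usable estimate for it, and a P value that depends on which test of the same model is read off.

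**Working it through.** **Inputs.** Total size 128, two arms and α = 0.05 are from the article. The allocation ratio is not stated, so 1:1 is an assumption. Event rates are not given, so a range is shown.

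**The plan's own figure first.** The sample is meant to "detect a between-group effect size (ES) of d = 0.50" with power "of 80% and an alpha of 0.05 (calculated using PASS 12"). The normal approximation gives n = 2(1.960 + 0.842)²/0.5² = 62.8, so 63 per arm. The noncentral t gives 63.77, so 64 per arm, 128 in total, with power 80.1%. The stated 128 reproduces with a two-sided test and equal arms, which supports taking 64 per arm.

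**Chance of an empty arm.** P(no events in a given arm) = (1 − p)^64.

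| True rate p | 0.5% | 1% | 2% | 3% | 5% | 10% |
|---|---|---|---|---|---|---|
| P(no events) | 73% | 53% | 27% | 14% | 4% | 0.1% |

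**What the model returns for 0/64 versus 6/64.**

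- Wald: after 20 Newton-Raphson steps the log odds ratio is 18.93 (odds ratio about 1.7 × 10⁸) with SE 5024. z = 18.93/5024 = 0.0038, so P = 0.997. The P value stays at 0.997 for every count from 1 to 10 against 0.
- Likelihood ratio: the log-likelihood with separate rates is 6 ln(6/64) + 58 ln(58/64) = −19.91. With a common rate it is 6 ln(6/128) + 122 ln(122/128) = −24.22. G² = 2 × 4.31 = 8.61 on 1 df, so P = 0.003.
- Fisher: with equal arms the two tails are equal. One tail is C(64,6)/C(128,6) = 0.0138, so P = 2 × 0.0138 = 0.028.
- Mid-P: the observed table gets half weight, so P = 2 × 0.5 × 0.0138 = 0.014.
- Firth-penalised logistic regression: odds ratio 14.3, P = 0.011.

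| Events | Wald P | Likelihood-ratio P | Fisher P | Firth P |
|---|---|---|---|---|
| 0 vs 3 | 0.997 | 0.040 | 0.244 | 0.107 |
| 0 vs 4 | 0.997 | 0.017 | 0.119 | 0.051 |
| 0 vs 6 | 0.997 | 0.003 | 0.028 | 0.011 |
| 0 vs 8 | 0.997 | 0.0007 | 0.006 | 0.0025 |

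With 51 per arm (an assumed 20% loss), 0 versus 6 gives Wald 0.997 and Fisher 0.027, so the result does not depend on full retention.

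**True size of each test.** This comes from full enumeration of two binomials with n = 64, equal true rates and nominal 5%. Wald is counted as non-significant when an arm is empty.

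| Common rate | Wald | Likelihood ratio |
|---|---|---|
| 2% | 0.0% | 7.6% |
| 3% | 0.0% | 9.3% |
| 5% | 0.6% | 7.9% |

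**Power, same enumeration, 1% versus 10%.** Wald 13%, Fisher 45%, mid-P 59%. The likelihood-ratio test reaches 75%, but it does not hold its level at rates of 2 to 5%.

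**Where no arm is empty.** 1 versus 8 gives Wald 0.041 and Fisher 0.033; 2 versus 10 gives 0.028 and 0.030. Conditional on no empty arm, Wald power is slightly above Fisher's: 26.6% against 24.7% for 1% versus 10%, and 55.8% against 50.3% for 3% versus 15%. The Wald shortfall therefore comes from tables with an empty arm.

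**The case against.** The strongest reply is that nothing here is stated wrongly. Logistic regression is a normal choice for a binary outcome. The article does not commit to a Wald test, and a fallback for empty cells is commonly left to an analysis plan that is not shown. The failure would also be conspicuous: nobody would overlook an odds ratio of 1.7 × 10⁸ with an SE of about 5000. Much of this stands, and it is why the point is minor. It does not remove the point, because the article does name a method and a threshold, and choosing the likelihood-ratio test instead of Wald does not repair it. That test rejects too often at rates of 2 to 5%.

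Several stronger readings are tempting but not supported:

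- A reader might infer that these effects will be sparse. The article gives no rate, and its Discussion says that very little is known about such effects. An empty arm is a real prospect at about 3% or below and negligible at 10%. An item counted as present at any agreement need not be rare.
- A reader might infer that the plan would report a harm signal as P near 1, and so leans towards safety. That holds only for Wald with an empty arm. The likelihood-ratio test errs the other way.
- A reader might infer that Wald is badly underpowered for rare events in general. Once empty arms are excluded it does no worse than plain Fisher.
- A reader might extend the point to χ2 tests on four-category INEP items. The article does not say that single items will be analysed that way.
- A reader might extend it to symptom deterioration. The sentence at issue covers only the other negative effects.

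Therapist-related items need separate care. The psychoeducation arm has no therapist support, so a near-zero count there is largely structural. Usual care could supply a few endorsements. An exact test would give a valid P value but would not make that comparison very informative.

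**Conclusion.** The point holds in conditional form. If a binary other negative effect is rare, the stated method is unreliable under either common test. With an empty arm it has no finite odds ratio and a Wald P of about 1. The likelihood-ratio P responds to the signal, but its true size is about 8 to 9% at equal rates of 2 to 5%. For 0 versus 6 events the same model gives 0.997 or 0.003, against 0.028 by Fisher and 0.014 by mid-P.

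This rests on 64 per arm (1:1 assumed), on a model with treatment arm as the only covariate, and on true rates of a few percent or less, which the article neither states nor rules out. How many outcomes are affected is unknown, because no rule for making INEP items binary is given. The outcomes are secondary. This is a minor improvement that is worth making because it costs little.

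**What to change.** Replace the logistic-regression clause for binary other negative effects with the following. Report the number of events and participants in each arm, and the risk difference with a score-type 95% confidence interval (Newcombe or Miettinen-Nurminen). Test with Fisher mid-P or Boschloo. If a model is wanted, use Firth-penalised logistic regression with profile-likelihood limits.

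Add that safety will not be inferred from P >0.05, and that the upper confidence limit will be read instead. Even 0/64 is compatible with a true rate of up to 1 − 0.025^(1/64) = 5.6% (two-sided exact limit).

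The cost is a change of wording before unblinding, a little more analysis work, and possibly software beyond SPSS 20. Plain Fisher would be conservative, which is the reason for preferring mid-P or Boschloo.
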